### 1.1 Evidence for Why This Research is Needed Now

The ‘holy grail’ of antimicrobial stewardship is to ensure the minority of patients needing treatment are given the shortest course of the narrowest spectrum antibiotic possible, while preventing unnecessary exposure among the majority unlikely to benefit, i.e. precision prescribing. The vast majority of stewardship interventions currently available aim to reduce overall prescribing, with only a handful of validated tools available to support precision prescribing in primary care.

Given that a significant proportion of RTIs managed in primary care are viral, it is plausible that a POCTRM providing accurate results quickly could improve prescribing. Accuracy depends on both the quality of the sample and equipment test performance. Lower respiratory tract sampling is not relevant for many community-acquired RTIs and, where it is, may not be practical. Throat and nose sampling is universally available, acceptable, and equivalent to nasopharyngeal samples, even when self-collected by patients. However, the main disadvantage of throat/nose sampling is that the common bacteria causing respiratory infections (*S. pneumoniae*, *M. catarrhalis* and *H. influenzae*) also reside harmlessly in the upper respiratory tract i.e. the nose and throat are not sterile. The resulting false positive results mean manufacturers do not include these microbes in upper respiratory tract panels. Respiratory viruses may also harmlessly reside in the upper respiratory tract, but less commonly. While there is currently no way to distinguish ‘commensal carriage’ from infection at the time of testing, patients with infection would be expected to experience worse outcomes, so measuring patients’ subsequent illness trajectory and response to antibiotics is important.

There is also evidence that microbiologically informed antibiotic prescribing could improve patient outcomes. Well-conducted RCTs consistently demonstrate clinically unimportant improvements in symptom severity and duration, suggesting there could be (as yet) unidentified sub-group/s experiencing clinically important benefits, and two studies suggest that patients from whom bacteria are isolated and given antibiotics have shorter illnesses compared to those not given antibiotics.

Moreover, our research shows that the detection of some upper respiratory tract microbes is associated with more prolonged illness and more severe symptoms at days 2 to 4, suggesting that detecting microbes could help manage patient expectations for subsequent illness trajectory and could help identify subgroups more (and less) likely to benefit from antibiotic (antiviral) treatment.

We considered multiplex systems would provide more clinical certainty than single or duplex POCTRMs systems. We are aware of three multiplex POCTRMs manufacturers: bioMérieux (Biofire® Respiratory 2.1), GenMark (ePlex new respiratory pathogen) and Qiagen (QIAstat-Dx Respiratory panel). The bioMérieux

system will be used in the RAPID-TEST trial because of its: high test accuracy, established technology (since 2011), fastest time-to-result (45 minutes compared to 1-2 hours), lowest price per test and because we used the same system in our feasibility study.

There is currently insufficient evidence regarding the safety, efficacy, or mechanism of action, let alone clinical and cost effectiveness, to recommend use of POCTRMs in primary care. Efficacy studies are urgently needed to address these issues using randomised controlled designs, as well as qualitative methods to understand clinician and patients' perceptions of the tests. The RAPID-TEST trial will show whether using multiplex POCTRMs in primary care could safely reduce the unnecessary use of antibiotics, and the beliefs that sustain unnecessary use, thereby reducing the public AMR risk. We will also show whether POCTRM use affects patient outcomes, antiviral prescribing, re-consultations and future consultations for RTIs. Results will inform the design of future pragmatic studies to investigate clinical and cost-effectiveness of POCTRMs in primary care.

## 2. AIMS AND OBJECTIVES

### 2.1 Aim

To evaluate the use of a rapid POCTRM for suspected RTIs in primary care.

### 2.2 Objectives and Outcomes

All objectives and their associated outcomes are listed in Tables 1 to 3.

**Table 1: Clinical Objectives and Outcome Measures**

| Objective                                                                                                                                                                                                                                                                                                                    | Outcome Measure                                                                                        | Source and published reference (where applicable)                                |
|------------------------------------------------------------------------------------------------------------------------------------------------------------------------------------------------------------------------------------------------------------------------------------------------------------------------------|--------------------------------------------------------------------------------------------------------|----------------------------------------------------------------------------------|
| Primary clinical objective
To investigate whether the use of a rapid POCT RM can reduce same-day antibiotic prescribing for children and adults presenting to primary care with respiratory infections where the Study Clinician and/or patient believes antibiotic treatment is, or may be, necessary. | Antibiotic prescribing (including delayed prescribing) for a RTI at Appointment Two (Step 6, Figure 1) | Study Clinician/Study Champion completed REDCap data                             |
| Key secondary clinical objective
To investigate whether the use of a rapid POCT RM changes participant reported symptom severity on days 2 to 4 A                                                                                                                                            | Mean symptom severity on Days 2 to 4 A                                                      | Trial Diary  completed daily by participant                         |
| Other secondary clinical objectives
To investigate whether the use of a rapid POCT RM changes:                                                                                                                                                                                                          |                                                                                                        |                                                                                  |
| 1. Participant (or parent/carer if the participant is <16 years) confidence in the clinical management of the infection                                                                                                                                                                                                      | See Appendix 1 (Participant Views question 5)                                                          | Participant views at Step 7 (Figure 1). For published references see Appendix 1. |

| Objective                                                                                                                                                                               | Outcome Measure                                                                                                                                                                                                                                                                                                                                                                                                                                                      | Source and published reference (where applicable)                      |
|-----------------------------------------------------------------------------------------------------------------------------------------------------------------------------------------|----------------------------------------------------------------------------------------------------------------------------------------------------------------------------------------------------------------------------------------------------------------------------------------------------------------------------------------------------------------------------------------------------------------------------------------------------------------------|------------------------------------------------------------------------|
| 2. Duration of moderately bad (or worse) symptoms                                                                                                                                       | Last day on which any symptom was recorded as “moderately bad” or worse                                                                                                                                                                                                                                                                                                                                                                                              | Trial Diary  completed daily by participant               |
| 3. Time to return to usual activities                                                                                                                                                   | 
Length of time to return to usual activities. This will be defined as per the ALICE trial:
 
 
Participants ≥16 years as the last day on which they mark “Unable to do usual activities” AND “Fever” as no more than “slight problem”.
 
Children <16 year as the last day on which they mark “Child not themselves/more clingy than usual” AND “Fever” as no more than “slight problem”
 
 | Trial Diary  completed daily by participant               |
| 4. Overall symptom duration                                                                                                                                                             | Last day prior to all symptoms recorded as zero for two consecutive days                                                                                                                                                                                                                                                                                                                                                                                             | Trial Diary  completed daily by participant               |
| 5. The proportion with new or worsening symptoms ≤28 days                                                                                                                               | Any new symptoms or worsening of pre-existing symptoms                                                                                                                                                                                                                                                                                                                                                                                                               | Trial Diary  completed daily by participant               |
| 6. The proportion consulting after Appointment Two and ≤28 days for RTI (with/out evidence of it being for the same illness, with/out evidence of the same illness having deteriorated) | Documentation of any RTI related consultation (in and out of normal office hours) after Appointment Two and ≤28 days, whether for the same symptoms /illness as the recruitment consultation with/out documentation that symptoms are getting worse                                                                                                                                                                                                                  | Retrospective collection from PCMR at least 2 months after recruitment |
| 7. The proportion with hospital admissions for respiratory infections ≤28 days                                                                                                          | Evidence of any hospital admission for a respiratory infection in the medical records ≤28 days                                                                                                                                                                                                                                                                                                                                                                       | Retrospective collection from PCMR at least 2 months after recruitment |
| 8. The quantity and timing of antibiotic and antiviral prescribing after Appointment Two and ≤28 days                                                                                   | Name, strength, frequency and quantity of antibiotics and antivirals prescribed after Appointment Two and ≤28 days                                                                                                                                                                                                                                                                                                                                                   | Retrospective collection from PCMR at least 2 months after recruitment |
| 9. Number of days on which antibiotics and antivirals are consumed ≤28 days                                                                                                             | Name of antibiotic and antiviral, and number of times per day the medicine was consumed                                                                                                                                                                                                                                                                                                                                                                              | Trial Diary  completed daily by participant               |

| Objective                                                                                                                       | Outcome Measure                                                                           | Source and published reference (where applicable)                  |
|---------------------------------------------------------------------------------------------------------------------------------|-------------------------------------------------------------------------------------------|--------------------------------------------------------------------|
| 10. Participant (or parent/carer if the participant is <16 years) intention to consult for similar future illnesses at 2 months | See Appendix 1 (Participant views questions 7 and 8)                                      | Questionnaire completed by participant 2 months post-randomisation |
| 11. The number of respiratory infection consultations >28 days and ≤6 months                                                    | Documentation of any consultation (in and out of normal office hours) ≤6 months for a RTI | Retrospective collection from PCMR at 6 months post-randomisation. |

A Day 1 is the day of randomisation

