### **6.9 Follow-Up**

The Trial Diary will be completed daily by the participant until their symptoms resolve (defined as all symptoms being rated zero for two days in a row) or up to day 28, whichever comes first. The central trial team will contact participants regularly via email, text or phone to support completion of the Trial Diary. Completed paper versions of the Trial Diary should be returned to BTC. Participants will be advised that if their symptoms have not resolved by Day 28, or if they have any concerns before Day 28, they should contact their GP practice for further advice.

Participants (or parent/carer if the participant is <16 years) will be followed-up with a questionnaire at 2 months post-randomisation which will collect beliefs and intention to consult for similar future illnesses (see Appendix 1, Participant Views questions 6 and 7). Up to two reminders will be sent for cases where the questionnaires are not returned. Questionnaires may be completed with the participants over the phone, and the data entered by the central trials team, if required. In addition, data on any further GP consultations for RTIs will be collected from their PCMR at 2- and 6- months after randomisation. For those participants randomised in the later stages of Summer 2, there will be a shorter follow-up period to ensure that all follow-up is completed 2 months after recruitment has finished.

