### 2.10.2. CLINICAL SECONDARY OUTCOMES

**Participant-completed symptom diaries** at baseline (day 1, pre-randomisation) and for 28 days afterwards (first post-randomisation completion on day 1 after appointment 2). Ten symptoms were completed by all participants: blocked nose, fever, shortness of breath, phlegm, wheeze, eating or drinking less than normal, disturbed sleep, ear pain and change in voice. Those age 16+ years completed four further symptoms: sore throat, muscle facial or head aching or pain, sweats or chills, and unable to do usual activities e.g. work school childcare etc. Those age under 16 years completed one additional item: child not themselves or more clingy than usual. Each item was responded to using the following seven-point scale:

- 0 = Normal/not affected
- 1 = Very little problem
- 2 = Slight problem
- 3 = Moderately bad
- 4 = Bad
- 5 = Very bad
- 6 = As bad as it could be

Participants are instructed to stop completing the diary once they have two consecutive days for which all symptoms are rated at zero, or once 28 days have been completed.

For any diary days that have been partially completed, with at least one symptom completed, symptoms left blank will assumed to be scored as zero (i.e. the symptom is completely resolved). Any days with no symptoms rated will be considered as missing data.

In addition participants were asked to record in the daily diaries if they were taking an antibiotic, which one, and how many doses were taken each day.

The following measures were derived from participant-completed symptom diaries:

| Diary measures                                                                         | Type       | Outcome detail                                                                                                                                                                                                                                                                                                                               |
|----------------------------------------------------------------------------------------|------------|----------------------------------------------------------------------------------------------------------------------------------------------------------------------------------------------------------------------------------------------------------------------------------------------------------------------------------------------|

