| Mean symptom severity on days 2 to 4
(KEY SECONDARY OUTCOME)                        | Continuous | Each day's responses will be converted to a mean score = sum of responses divided by the listed number of symptoms.                                                                                                                                                                                                                          |
| Duration of moderately bad (or worse) symptoms                                         | Ordinal    | Longest continuous spell (in days) with one or more symptoms rated $\geq 3$ , concluding with two days where all symptoms are rated $< 3$ .                                                                                                                                                                                                  |
| Number of days to return to usual activities (adult participants $\geq 16$ years only) | Ordinal    | For participants with "Unable to do usual activities" rated $\geq 3$ at baseline, the number of consecutive days that item is rated $\geq 3$ , followed by two days where it is rated $< 3$ . For participants with "Unable to do usual activities" rated as $< 3$ at baseline, their duration will be zero.                                 |
| Number of days to return to usual activities (child participants $< 16$ years only)    | Ordinal    | For participants with "Child not themselves / more clingy than usual" rated $\geq 3$ at baseline, the number of consecutive days that item is rated $\geq 3$ , followed by two days where it is rated $< 3$ . For participants with "Child not themselves / more clingy than usual" rated as $< 3$ at baseline, their duration will be zero. |
| Overall symptom duration                                                               | Ordinal    | The number of consecutive days one or more symptoms are rated $> 0$ , concluding with two days where all symptoms are rated 0.                                                                                                                                                                                                               |

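### Time to return to usual activities: the protocol's rule runs in the wrong direction, and the SAP's different rule drops the fever condition without explanation

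*Combined protocol and SAP*

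**What the plan says.** Protocol section 2.2, Table 1, other secondary clinical objective 3 names the outcome and attributes its definition to an earlier primary care trial in influenza-like illness: "Length of time to return to usual activities. This will be defined as per the ALICE trial". For participants aged 16 and over it is taken "as the last day on which they mark “Unable to do usual activities” AND “Fever” as no more than “slight problem". For under-16s it is taken "as the last day on which they mark “Child not themselves/more clingy than usual” AND “Fever” as no more than “slight problem". The SAP's response scale in section 2.10.2 has "2 = Slight problem", so the condition means both items scored 0 to 2.

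Protocol section 6.9 has the diary completed "until their symptoms resolve (defined as all symptoms being rated zero for two days in a row) or up to day 28", taking the earlier of the two. The SAP agrees: "Participants are instructed to stop completing the diary once they have two consecutive days for which all symptoms are rated at zero", with Day 28 as the limit.

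The diary-measures table in SAP section 2.10.2 derives the outcome differently. For those at 3 or more at baseline on the activity item (adults) or the child item (children), it counts the consecutive days that item stays at 3 or more, ended by two days below 3. Otherwise, for adults: "For participants with 'Unable to do usual activities' rated as $< 3$ at baseline, their duration will be zero". The children's rule is the same. Fever does not appear. SAP Table 3 reports the result as a difference in means, with adults and children in separate rows. The SAP says that it summarises protocol version 3.0 and gives no reason for the change. The protocol's amendment history lists no change to this outcome.

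**The concern.** A time to recovery should be the first day in the recovered state, or the last day in the unrecovered state. The protocol takes the last day in the recovered state. Once a participant has recovered, each further day without relapse still qualifies, so the value is set by when the diary stops, not by when function returned. The row above it, duration of moderately bad symptoms, uses the same phrase correctly because it refers to the bad state: "Last day on which any symptom was recorded as “moderately bad” or worse".

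The SAP repairs the direction but also changes what is measured. One prespecified outcome now has two public definitions under one name. The SAP version scores some participants as having no limitation although the protocol's condition is unmet, or although they become limited after randomisation.

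**Working it through.** No sample size, power or alpha is tied to this outcome, so there is no stated figure to reproduce. The check applies each written rule to the same diaries.

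**Inputs from the documents.** Recovered means both items at 2 or less. The diary ends on the second of two consecutive all-zero days, or on Day 28. The SAP count ends when two consecutive days are below 3, and it is zero if the baseline item is below 3.

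**Assumptions.** The six diaries are invented for illustration. They are complete, and days are counted from the Day 1 entry after randomisation.

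**Protocol rule in general.** Protocol objective 4 defines overall symptom duration as the last day before two consecutive all-zero days. If that day is D, the diary closes on D + 2. Both items are zero on that day, so the literal value is D + 2 for every participant who resolves. If symptoms are unresolved on Day 28 and both items are 2 or less that day, the value is 28.

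**Diaries**
- A: activity 3 or more to Day 3, fever 3 or more to Day 5, mild cough to Day 14.
- B: as A, with cough to Day 21.
- C: as A, with cough never resolving.
- D: activity 3 or more to Day 10, fever to Day 5, other symptoms to Day 12.
- E: activity 2 at baseline, 3 or more on Days 2 to 6, no fever, other symptoms to Day 10.
- F: activity 3 or more to Day 3 and again on Days 26 to 28, no fever.

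Baseline activity is 4 in all except E.

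| Diary | Protocol as written | First of two consecutive days with both items 2 or less | Last day either item 3 or more | SAP rule | SAP rule with fever added |
|---|---|---|---|---|---|
| A | 16 | 6 | 5 | 3 | 5 |
| B | 23 | 6 | 5 | 3 | 5 |
| C | 28 | 6 | 5 | 3 | 5 |
| D | 14 | 11 | 10 | 10 | 10 |
| E | 12 | 7 | 6 | 0 | 0 |
| F | 25 | 4 | 28 | 3 | 3 |

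**Reading the table**
- A to C have identical activity and fever. The protocol value moves from 16 (14 + 2) to 23 (21 + 2) to 28 solely because of a cough.
- In A the SAP rule is 5 − 3 = 2 days shorter than the activity-plus-fever count. In D, where activity limitation outlasts fever, the two agree at 10.
- In E, Day 1 qualifies but Day 2 does not, so the first qualifying pair starts on Day 7 (6 + 1). The SAP gives 0 despite five limited days. Adding fever does not help, because the zero comes from the baseline rule.
- By the same rule, a participant with fever 3 or more but activity below 3 at baseline scores 0 in the SAP although the protocol's condition is unmet.
- In F either item is still at 3 or more on the final day, so the protocol rule gives 25, not the diary end of 28. F also shows that the two natural corrections, first sustained recovered day and last limited day, match (one day apart) only when there is no relapse.

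**The case against.** The strongest reply is that the protocol wording is a drafting slip unlikely to reach the results. Protocol section 10.2 defers to a detailed SAP, which supplies its own derivation and results rows. The SAP rule uses the very item that names the outcome. Fever is a diary symptom at all ages, so it already enters the days 2 to 4 severity score, duration of moderately bad symptoms, overall duration, and new or worsening symptoms. Whether an activity outcome should also require settled fever is partly a matter of preference. The cited trial's own definition cannot be checked from these documents, so it is open which version matches it.

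All of this stands, and it rules out several stronger readings that a reader might infer:
- *Neither document yields the named outcome.* The SAP rule is a usable activity-only measure; it fails only to reproduce the protocol's composite.
- *The protocol rule always equals the end of the diary.* Diary F is an exception.
- *A harm signal from prolonged fever is lost.* Other diary outcomes capture it.
- *The treatment effect is biased by a known amount.* If 5% to 20% of participants had 2 to 4 days of fever with activity below 3 at baseline (assumed, not from the documents), the arm mean would be understated by 0.05 × 2 = 0.1 to 0.20 × 4 = 0.8 days. That subgroup is defined before randomisation and expected to be balanced, so this says nothing about the between-group difference.

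The reply does not remove the incorrect definition in the protocol, the undeclared change in the SAP, or the automatic zero.

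**Conclusion.** The point holds in a bounded form. The protocol definition is in the wrong direction for both age groups and, read literally, measures diary length in everyone who resolves. The SAP definition has the right direction but is a different, activity-only outcome. It gives a shorter time when fever outlasts activity limitation (3 against 5 limited days in diary A), and zero for anyone below 3 at baseline whatever follows. The general results follow from the written rules, given complete diaries; the individual values rest on invented diaries. How often these patterns occur is not stated, so the size and direction of any effect on the treatment comparison cannot be determined. The change is worth making because a stated rule gives a wrong value and the two documents disagree, but the primary and key secondary results are untouched.

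**What to change.** 1. In protocol Table 1, objective 3, replace the last day by the first of two consecutive days on which the activity (or child) item and fever are both 2 or less. Without relapse this is the day after the last day on which either item is 3 or more. The rule should say how a relapse is handled.
2. In SAP section 2.10.2 use the same activity-plus-fever rule on one stated time scale: either the day number of return (6 in diary A) or the count of days before it (6 − 1 = 5). Alternatively, amend the protocol to activity-only and declare the change. Either version can be kept as a supplementary row.
3. Assign zero only if the condition is met at baseline and stays met over the following diary days, with that period defined. Score a participant who becomes limited later to the end of that limited spell.
4. State the change and its reason in the final report, as SAP section 1 already promises for SAP amendments.

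The cost is one line in the protocol and one derivation rule in the SAP. Fever and both age-specific items are already in the diary, so no new data are needed.
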